
### Secondary outcomes

Physical function: The Timed Up and Go test (TUG) will be used to assess the physical function performance of the participants. Previous study reported that the TUG is simple, reliable and valid measurement for assess the physical performance of the KOA [39, 40]. During TUG test, the participants will be required to stand up from a standard chair (40 cm height), walk 3 m, turn around, walk back, and sit down again. The test will be performed 3 times and record with chronograph.Walking function: The gait analysis of the self-selected speed walking will be used to assess the walking function for KOA. The gait analysis is chosen as functional measures of walking, due to the quantitative and systematic evaluation methods, could more comprehensively assess the changes of walking function than the graded assessment scale [41, 42]. Such as, the knee adduction moment can effectively reflect the degree of pressure imbalance between the medial and lateral compartments of the knee joint [42]. Full body three-dimensional kinematics and ground reaction forces are collected by a 10-camera infrared motion capture system (Vicon Motion Systems, Oxford, United Kingdom) and the force platform (Kistler Instruments AG Corp., Switzerland), respectively. The human biomechanical model is built based on Visual 3D (C-Motion, Inc., United States). The gait analysis outcomes will be included: temporospatial parameters (e.g., step length, step velocity, single support time), the range of motion and knee adduction moment.Inflammatory factor levels: The fasting venous blood, synovial fluid of the knee joint will be collected from the patients for analysis the inflammatory factor levels [43, 44]. • The inflammatory factor in the venous blood: 5 ml of fasting venous blood will be collected from the patients in the morning with routine local disinfection. The Interleukin-1 β (IL-1 β), interleukin-6 (IL-6), and vascular endothelial growth factor (VEGF) will be measured by Enzyme-Linked Immunosorbent Assay (ELISA). Furthermore, erythrocyte sedimentation rate (ESR) was measured by Westergren method. • The inflammatory factor in the synovial fluid: 2 mL of synovial fluid will be withdrawn from the joint cavity by puncturing the syringe just above the patella and lateral quadriceps femoris. For those who could not be extracted successfully due to the lack of joint fluid, 0.9% chlorinated steel injection (2 mL) will be injected into the joint cavity to move the knee joint and then extracted [43]. The IL-1 β, IL-6 and tumor necrosis factor α (TNF-α) will be measured by ELISA.Quality of life: The 36-Item Short Form Health Survey (SF-36) will be used to comprehensively evaluate the quality of life across broad physical and emotional health domains of the participants. Previous study reported that the SF-36 is easy to use, acceptable to patients, and fulfills stringent criteria of reliability and validity [45, 46]. The SF-36 questionnaire includes eight multiple-item subscales, the score on each SF-36 subscale ranges between 0 and 100, and greater score indicates better quality of life.Knee structural evaluation: The knee structural changes will be evaluated by 3 Tesla Philips MRI scanners and a sense coil for the following sequences: transverse 3D TRUFISP and coronal and sagittal fat saturated protondensity. • Volume of patellofemoral cartilage: The cartilage area was manually segmented from the nearby bone and soft tissue in the TRUFISP 3D sequence. Subsequently, the volume of the cartilage was determined by multiplying the sum of the cartilage area in all the images by the slide thickness, utilizing 3D slicer software [47]. • Effusion-synovitis: The presence of intra-articular fluid-equivalent signal on the proton density-weighted images was used to define effusion-synovitis [48]. A semi-automated segmentation technique was employed to measure the volume of effusion-synovitis. The final 3D volume rendering was created using 3D Slicer, a free open-source imaging software (version 4.10, National Alliance of Medical Image Computing, NA-MIC) [49].

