### Outcome measures

Outcome measures will be assessed by profession rehabilitation assessor, biochemical analyst and ultrasound doctor at baseline (T1) before intervention, 6 weeks (T2) and 12 weeks (T3) during intervention, and 3 months (T4) and 12 months (T5) during follow-up period. The demographic and clinical characteristics of the all participants will be collected at the time of enrollment.

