### Statistical analysis

All statistical analyses will be performed with IBM SPSS (Version 22.0, Chicago, IL, USA) by statisticians who are blinded to the group allocation. The outcomes analyses will be performed on an intention-to-treat basis. For the missing data, several sensitivity analyses will be conducted to evaluate their effects on the results. The Shapiro–Wilk will be used to test the normal distribution of the continuous variables for demographic and outcome measures. Continuous variables will be described as mean ± SD for normal distributions or median for non-normal distributions, categorical variables will be described as frequency. The χ^2^ test or Fisher’s exact test will be used to examine the comparisons between the four groups for categorical variables. When the normality of data distribution is found, two-way of variance with repeated measures will be applied to examine the main effects of the group and the time factor and group-time interaction effects. A simple effect post hoc analysis will be conducted, when time-group interaction is significant. Additionally, if homogeneity is not found, a linear mixed model will be adjusted for gender and KL grade. To mitigate bias and potential confounding variables, the propensity score matching (PSM) method will be employed [50]. Significant level for all tests will be set at 0.05 for all statistical tests and corrected for multiple comparisons using the Bonferroni-adjusted method, and 95% confidence interval will be reported.

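### Neat and saline-diluted synovial samples go to the same cytokine assay with no stated flag, marker or correction, so a change of sampling route can look like a cytokine change

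*Protocol article*

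**What the plan says.** The protocol article, Secondary outcomes, Inflammatory factor levels, sets two sampling routes for one outcome.

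- **Standard route:** "2 mL of synovial fluid will be withdrawn from the joint cavity by puncturing the syringe".
- **Fallback route:** "For those who could not be extracted successfully due to the lack of joint fluid, 0.9% chlorinated steel injection (2 mL) will be injected"; after some movement of the knee, the liquid is drawn off again as the sample.
- **Assay, with no distinction between routes:** "The IL-1 β, IL-6 and tumor necrosis factor α (TNF-α) will be measured by ELISA".

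The garbled name of the 0.9% solution is read here as sodium chloride, as in the article's description of the placebo. The point does not depend on that reading, because any 2 mL of added liquid dilutes the sample.

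In the same section, effusion is an outcome in its own right: "A semi-automated segmentation technique was employed to measure the volume of effusion-synovitis".

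Outcomes are assessed at baseline and at "6 weeks (T2) and 12 weeks (T3) during intervention, and 3 months (T4) and 12 months (T5) during follow-up period". Table 1 is not shown, so the visits with synovial sampling cannot be confirmed.

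The Statistical analysis section tests group, time and group-by-time effects. Its only named adjustment, and only if homogeneity is not found, is that "a linear mixed model will be adjusted for gender and KL grade". Neither that section nor Data collection and management mentions the sampling route.

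**The concern.** A neat sample and a washout sample from the same knee on the same day would give different readings for the same biology. The gap is not a constant. It depends on how much fluid was left in the joint, and the article does not say that this volume, or the recovered volume, is recorded.

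The error is also not plain noise. Washout is used when fluid is scarce, and the amount of fluid in the knee is close to what the MRI effusion-synovitis outcome measures. One outcome therefore partly decides how another is measured. A knee with enough fluid at baseline and too little at week 12 switches route, and its recorded cytokines fall through dilution alone.

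At stake is the reading of the synovial cytokines. The trial's rationale combines a biochemical with a biomechanical mechanism, and the Discussion names inflammatory factors in blood and synovial fluid among the strengths of the outcome set. If the sampling route is not recorded when the sample is taken, no later analysis can recover it.

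**Working it through.** The plan gives no figure of its own to reproduce here.

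**Inputs from the article:** 2 mL target sample; 2 mL injected when aspiration fails for lack of fluid; one ELISA for both routes.

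**Assumed inputs (not in the article):** residual fluid v of 0.25 to 1.5 mL, below the 2 mL target because washout is for knees where the standard sample failed; full mixing; the same v in every washed knee compared; the washout shares below; a coefficient of variation of 50% for the simulation.

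**Step 1. Dilution in one sample.** Measured/true = v/(v+2), and the factor needed to undo it is (v+2)/v.

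| v (mL) | Measured/true | Correction factor |
|---|---|---|
| 0.25 | 0.25/2.25 = 0.11 | 9.0 |
| 0.5 | 0.5/2.5 = 0.20 | 5.0 |
| 1.0 | 1/3 = 0.33 | 3.0 |
| 1.5 | 1.5/3.5 = 0.43 | 2.3 |

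A knee that switches from neat to washout, with its true level unchanged, would appear to fall by 57% (1 − 0.43) to 89% (1 − 0.11). The correction factor runs from 2.3 to 9.0, so no single constant can repair the data.

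**Step 2. Effect on a mean.** Set the true level to 1 everywhere and let p be the share of washout samples. The mean is (1 − p) + p·v/(v+2). Compare p = 20% with p = 40%:

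| v (mL) | Mean at 20% | Mean at 40% | Apparent difference |
|---|---|---|---|
| 0.25 | 0.822 | 0.644 | −21.6% |
| 0.5 | 0.840 | 0.680 | −19.0% |
| 1.0 | 0.867 | 0.733 | −15.4% |
| 1.5 | 0.886 | 0.771 | −12.9% |

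With 20% against 60%, the range is −25.8% (v = 1.5) to −43.2% (v = 0.25). With 20% against 20%, it is 0%.

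The same arithmetic reads two ways. If 20% and 40% are two visits, it is a false time effect, even with balanced arms. If they are two arms at one visit, it is a false group difference.

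**Step 3. Effect on a test.** A simulation compared two arms of 42 with identical true levels, using a t-test on log concentrations at the 5% level (4,000 runs, v = 0.5 and 1 mL). The false-positive rate was:

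- 0.05 with equal shares of 20%;
- 0.31 (v = 1) to 0.40 (v = 0.5) with 20% against 40%;
- 0.81 (v = 1) to 0.92 (v = 0.5) with 20% against 60%.

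This shows the mechanism under assumed shares. It does not predict this trial's error rate.

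**The case against.** The strongest reply is that the article is silent rather than wrong. It does not say that uncorrected neat and washout values are pooled. A flag or correction could sit in a laboratory manual, the case report form, the analysis plan or the source cited for the flush, none of which is shown. That stands as far as it goes: uncorrected pooling is what follows if the text is applied as written, not a choice the article declares. It does not remove the point. The article spells out the flush in detail, sends both routes to one assay, and describes the measurement rule itself. Unlike a modelling detail, a route that was not recorded cannot be supplied later.

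A second reply is that one washout rule applies in all four arms, so equal shares produce no group difference. This is correct, and Step 2 shows it.

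A reader might infer the stronger claim that the active arms will show a false fall in cytokines, biasing the trial in favour of PRP or Tai Chi. The documents do not support that. They list effusion-synovitis as a measured outcome without stating an expected direction, and they give no washout shares. The PRP preparation and injection section also has joint fluid aspirated before injection, and the Interventions section keeps injection frequency and dose consistent between PRP and placebo in the four groups. Part of any change in fluid during treatment may therefore be common to all arms.

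Third, the reach is limited. WOMAC, acceptability, safety, TUG, gait, SF-36, MRI and the blood markers are untouched. IL-1 β and IL-6 are also measured in venous blood. TNF-α is listed for synovial fluid only, so it has no such back-up.

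**Conclusion.** The point holds as a flaw in a measurement rule for one group of secondary outcomes. As written, two sample types with different dilution feed one concentration outcome, and the choice between them depends on joint fluid, which is related to another trial outcome.

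A washout sample would read about 11% to 43% of the true value, assuming 0.25 to 1.5 mL of residual fluid and full mixing. The time effect is distorted if washout shares change over visits. The group or group-by-time effect is distorted only if shares differ by arm. The 13% to 22% apparent difference for shares of 20% against 40% is illustrative. The actual size and direction cannot be known from the article, and a bias towards the active arms should not be asserted. Synovial IL-1 β, IL-6 and TNF-α are the only results affected.

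**What to change.** - **Record** neat or washout for every synovial sample, and report the washout share by arm and visit.
- **Correct** each washout sample with a per-sample dilution marker and analyse the corrected concentrations. One example is the synovial-to-blood urea ratio. It needs blood from the same visit and rests on the assumption, for the laboratory to confirm, that urea is at the same level in blood and undiluted synovial fluid. The article already plans both specimens: "The fasting venous blood, synovial fluid of the knee joint will be collected from the patients for analysis".
- **Sensitivity analysis:** repeat the comparison on neat samples only. This should not be the main analysis, because it selects patients on joint fluid after randomisation, and the report should say so.
- **If no marker is assayed,** do not pool washout with neat values. Show the two separately and treat the synovial cytokine comparisons as exploratory.

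The cost is a routine assay on samples already collected, one field on the case report form and a few lines of analysis text. Synovial comparisons will be less precise, because correction factors of 2.3 to 9.0 also multiply assay error and the neat-only analysis uses fewer samples. Nothing about treatment changes.

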
### Data collection and management

The demographic, clinical characteristics, outcome measures, adverse events, and safety evaluations will be collected and recorded in the CRF. The outcome assessor fill-in relevant information timely and accurately according to the CRF requirement. The data check (e.g., checked against the CRF of the origin data, double-checking) will be conducted to ensure the data accuracy before electronic storage. The two research assistants who are blinded the study process will enter all the collected data into the data management system with a double entry method. In addition, they also will enter the real-time data into the Chinese Clinical Trial Registration Center. Access to the dataset will be restricted to the Clinical Trial Management and the Data Safety and Monitoring Board. Storage and disposal of research data hard copies will strictly follow the regulations and policies of the investigator’s institution and the study sites. In addition, serious adverse events will be reported to an independent Data Safety and Monitoring Board that will advise whether to continue, modify or stop the intervention. During the study process, to protect individual privacy before, the dataset will be stored, analyzed and archived in a pseudonymized manner.

### Statistical analysis

All statistical analyses will be performed with IBM SPSS (Version 22.0, Chicago, IL, USA) by statisticians who are blinded to the group allocation. The outcomes analyses will be performed on an intention-to-treat basis. For the missing data, several sensitivity analyses will be conducted to evaluate their effects on the results. The Shapiro–Wilk will be used to test the normal distribution of the continuous variables for demographic and outcome measures. Continuous variables will be described as mean ± SD for normal distributions or median for non-normal distributions, categorical variables will be described as frequency. The χ^2^ test or Fisher’s exact test will be used to examine the comparisons between the four groups for categorical variables. When the normality of data distribution is found, two-way of variance with repeated measures will be applied to examine the main effects of the group and the time factor and group-time interaction effects. A simple effect post hoc analysis will be conducted, when time-group interaction is significant. Additionally, if homogeneity is not found, a linear mixed model will be adjusted for gender and KL grade. To mitigate bias and potential confounding variables, the propensity score matching (PSM) method will be employed [50]. Significant level for all tests will be set at 0.05 for all statistical tests and corrected for multiple comparisons using the Bonferroni-adjusted method, and 95% confidence interval will be reported.

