### Sample size

The sample size will be determined based on the priori power analysis through G*Power software version 3.1.9.2 [26]. In the calculations, ANOVA repeated measures between factor will be chosen, effect size 0.25, alpha 0.05, power 0.80, number of groups 4, number of measures 5, and the sample size is calculated as 168. Taking into account a conservative anticipation of a 20% drop-out rate, the final sample size will therefore be 53 in each group, with a total of 212 subjects.

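### The main analysis is a normality-gated repeated-measures ANOVA which, unless missing values are imputed first, keeps only five-visit completers and so conflicts with the stated intention-to-treat basis

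*Protocol article*

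**What the plan says.** All of this is in the protocol article.

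- **Population** (Statistical analysis): "The outcomes analyses will be performed on an intention-to-treat basis".
- **Gate** (Statistical analysis): "The Shapiro–Wilk will be used to test the normal distribution of the continuous variables for demographic and outcome measures".
- **Main model** (Statistical analysis): "When the normality of data distribution is found, two-way of variance with repeated measures will be applied". The Abstract names the same repeated-measures analysis for every outcome measure, so it covers WOMAC, the primary efficacy outcome.
- **Mixed model** (Statistical analysis): "Additionally, if homogeneity is not found, a linear mixed model will be adjusted for gender and KL grade". This is the only place where the two stratification factors enter an outcome model. The word homogeneity is not defined.
- **Missing data** (Statistical analysis): "For the missing data, several sensitivity analyses will be conducted to evaluate their effects on the results". No handling is stated for the main analysis itself.
- **Software** (Statistical analysis): SPSS 22.0.
- **Visits** (Outcome measures): five, T1 (baseline) to T5 (12 months).
- **Expected loss** (Sample size): "Taking into account a conservative anticipation of a 20% drop-out rate", which takes 168 to 53 per group and 212 in total.

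**The concern.** The section makes two statements that do not fit together as written. Intention-to-treat means that the comparison rests on everyone randomised. A classical repeated-measures ANOVA needs a value at every level of the time factor, and the standard SPSS procedure deletes a patient with any missing visit. With five visits over more than a year, that makes it a completers analysis unless something is done to the data first. Sensitivity analyses can probe a primary estimate, but they do not change who is in it.

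What is at stake is the primary WOMAC comparison. Participants cannot be blinded to Tai Chi, so drop-out may plausibly differ between Tai Chi and non-Tai Chi arms. Aim 2 (B against C) and half of Aim 1 (D against B) compare exactly those arms.

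There is a second, independent weakness. The choice of model is made after looking at the outcome data. Whether the ANOVA is used depends on a significance test of normality. Whether gender and KL grade are adjusted for depends on a different, undefined check. Both could be fixed in advance at almost no cost.

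**Working it through.** **1. The plan's own figure.** Inputs from Sample size: 168 evaluable, 20% drop-out, four equal groups.

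168 / (1 − 0.20) = 210; 210 / 4 = 52.5, rounded up to 53; 53 × 4 = 212. The stated total reproduces.

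**2. Complete cases under that drop-out.** 212 × 0.80 = 169.6, so about 170 analysed and about 42 randomised patients left out. Since 170 exceeds 168, drop-out alone does not take the trial below its target.

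Missed visits among those who stay would lower this further. The protocol gives no rate, so this part is an assumption. With a proportion q missing at each of the four post-baseline visits, complete cases = 169.6 × (1 − q)^4:

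| q (assumed) | complete cases |
|---|---|
| 0 | 170 |
| 2% | 156 |
| 5% | 138 |

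**3. Size and direction of completer bias.** The article gives no correlation and no drop-out model, so this is illustrative. Assumptions: equal correlation 0.5 between visits; true difference 0.35 SD in favour of the Tai Chi arm; about 20% lost after week 6; where drop-out depends on outcome, the log-odds of leaving rise by 0.5 to 1.0 per SD of the week-6 score; otherwise drop-out is random. Very large simulated arms were used, so the differences shown are bias, not noise.

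| Outcome-dependent drop-out in | Completers | All observed visits |
|---|---|---|
| Tai Chi arm only | 0.40 to 0.44 SD | about 0.35 SD |
| both arms | 0.33 to 0.34 SD | about 0.35 SD |
| comparator only | 0.25 to 0.30 SD | about 0.35 SD |

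A separate set-up points the same way on size. It had two arms of 53, a true difference of 0.50 SD, drop-out after any post-baseline visit depending on the last score in both arms, and 82% to 86% completers. Completers gave 0.46 to 0.48 SD, and using all observed visits gave 0.50 to 0.51 SD.

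**4. The normality gate.** With normal data, k independent tests at 0.05 give at least one false rejection with probability 1 − 0.95^k:

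- k = 1: 0.05
- k = 5 (one per visit, groups pooled): 1 − 0.95^5 = 0.23
- k = 20 (four groups × five visits): 1 − 0.95^20 = 0.64. A simulation with correlated visits gave 0.638, so treating the tests as independent costs little.

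The article does not say which of these applies, nor whether one rejection closes the gate.

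**5. Adjustment.** Randomization, allocation concealment and blinding stratifies on gender and KL grade. The ANOVA is described with group and time only. The two factors appear only in the model reached when the homogeneity check fails, so adjustment for the design factors also depends on a pre-test.

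**The case against.** The strongest reply is that deletion of incomplete patients is nowhere written. The article says intention-to-treat and does not name the SPSS procedure, and an unseen full plan could impute before the ANOVA. That stands as a limit: a reader might infer that the primary analysis is certainly a completers analysis, and the document does not establish that. What remains is that the article names a method that needs complete data, mentions missing data only under sensitivity analyses, and states no step that reconciles the two.

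Other replies that stand:

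- **Power.** The 20% inflation already allows for losing drop-outs, and 170 is above 168. The counts of 156 and 138 rest on assumed intermittent misses.
- **Direction.** It is tempting to infer that completer analysis would flatter Tai Chi. That happens in one scenario only; the reverse, or almost no bias, is equally possible.
- **The 64%.** It holds only for twenty separate tests with any rejection decisive.
- **Homogeneity.** One might argue that a mixed model cannot cure the failure that triggers it. The text does not support this. The word could mean baseline comparability, equal variances or sphericity, and a mixed model with unstructured covariance does deal with unequal variances and correlations across visits. The fair criticism is only that the trigger is undefined.
- **No test named for non-normal outcomes.** An article may leave this to the analysis plan, so it is not counted here. The gate itself is stated, and is open to criticism.

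**Conclusion.** The point holds in a conditional form. As written, and absent imputation, the main analysis would use about 170 of 212 randomised patients, which does not match the intention-to-treat statement in the same section. The consequence is possible bias rather than lost power. For a true 0.35 SD, the completer estimate ranged from about 0.25 to 0.44 SD over the assumed mechanisms, against about 0.35 SD with all observed visits. Those figures rest on an assumed correlation of 0.5, an assumed strength of outcome-dependent drop-out, and drop-out that depends only on observed scores. They show what could happen, not what will.

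Separately, and without any assumption about missing data, the method and the adjustment for stratification factors are chosen by pre-tests on trial data. The chance that the normality gate fails on normal data lies between 5% and 64%, depending on a unit of testing that the article leaves open.

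This should be changed before the analysis is fixed, because it decides who is in the primary efficacy estimate and the remedy is cheap.

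**What to change.** 1. Make a linear mixed model for repeated measures the unconditional primary analysis of WOMAC and the other continuous repeated outcomes: REML, unstructured covariance over visits, and terms for group, visit, group-by-visit, gender and KL grade.
2. Include all randomised patients with any observed value, with baseline as one of the repeated measures, so that a patient seen only at T1 is not excluded.
3. Remove the Shapiro–Wilk and homogeneity triggers. Check residuals, and use robust standard errors or a transformation as sensitivity analyses.
4. State that the model assumes data missing at random, and name at least one missing-not-at-random sensitivity analysis in place of the present general sentence.
5. Bring the Abstract's description of the analysis into line.

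The cost is the rewording of a few sentences and slightly more analysis work. The mixed-model procedure is available in the software already named. The one real downside is reliance on missing at random, which step 4 makes explicit and tests.

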Therefore, the placebo-controlled, assessor-blinded randomized trial will be design in the present protocol, which will include group A (IAI-placebo), group B (IAI-PRP), group C (TC + IAI-placebo), and group D (TC + IAI-PRP). This protocol will allow to be achieve the study purpose as follows:

Aim 1: To examine the effectiveness and safety of combined IAI-PRP and TC for KOA treatment by comparing the group D vs B or C.

Aim 2: To compare the differences of efficacy between the IAI-PRP and TC in the KOA treatment by comparing the group B and C.

Aim 3: To provide high-quality evidence of PRP for KOA treatment by comparing the group B and A.

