## Methods/Design

### Study design

This protocol will be a placebo-controlled, assessor-blinded randomized trial, which will be included 12-week intervention and 1-year follow-up. This protocol will be conducted in accordance with the Standard Protocol Items: Recommendations for Interventional Trials (SPIRIT) [25]. A total of 212 patients diagnosed with KOA will be randomly and equally assigned into the group A (IAI-placebo), group B (IAI-PRP), group C (TC + IAI-placebo), and group D (TC + IAI-PRP). A brief flowchart of the entire study is shown in Fig. 1, and the schedule of events is provided in Table 1. The study protocol was approved by the Ethics Committee of Shanghai Seventh People’s Hospital (2022-7th-HIRB-067) and registered in the Chinese Clinical Trial Registry (ChiCTR2300067559).

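### The efficacy contrasts named in Aims 1 to 3 are reached only through a significant group-by-time interaction, which is not the test the trial is sized on

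*Protocol article*

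**What the plan says.** The Background section of the Protocol article states the aims as comparisons of named arms. Aim 1 is "To examine the effectiveness and safety of combined IAI-PRP and TC for KOA treatment by comparing the group D vs B or C"; Aim 2 compares B with C, and Aim 3 compares B with A.

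The Sample size section describes its calculation as "ANOVA repeated measures between factor will be chosen, effect size 0.25, alpha 0.05, power 0.80, number of groups 4, number of measures 5". That is the between-group main effect. It reports that "the sample size is calculated as 168" and, after allowing for 20% drop-out, "the final sample size will therefore be 53 in each group, with a total of 212 subjects".

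The Statistical analysis section tests group, time and group-by-time effects in a repeated-measures ANOVA. It then moves to comparisons between groups with one sentence: "A simple effect post hoc analysis will be conducted, when time-group interaction is significant". Elsewhere the section offers:

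- a linear mixed model as a fallback, with no contrasts named;
- a four-group chi-square or Fisher test for categorical variables;
- a general statement that multiple comparisons are Bonferroni-corrected, without saying how many.

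It specifies no follow-up to a significant group main effect and no unconditional test of the contrasts in the aims.

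**The concern.** The comparisons that define the trial's purpose are treated as post hoc and placed behind an omnibus test. That test differs from the one used for sizing, so the two can disagree. If the group effect is significant and the interaction is not, the text provides no pairwise efficacy result for WOMAC, neither an estimate nor a confidence interval. This matters most for Aim 2, PRP against Tai Chi, where the estimate and its interval are the answer whichever way the omnibus tests fall.

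The gate is also not needed for error control, because the same section already applies Bonferroni. A contrast must therefore clear two hurdles, and its power cannot exceed that of the Bonferroni test alone.

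**Working it through.** **Inputs from the protocol.** Four groups, five measures (baseline T1 plus T2 to T5), f = 0.25, alpha 0.05, power 0.80, 168 evaluable (168/4 = 42 per arm), 20% drop-out. **Assumed, because not stated:** the within-patient correlation ρ (shown from 0.3 to 0.9), compound symmetry, equal baselines, and an effect that is constant from T2 to T5.

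**1. Reproduce the stated sample size.** For the between factor, λ = f²·N·m / (1 + (m − 1)ρ) with 3 and N − 4 df. At N = 168 and ρ = 0.9, λ = 0.0625 × 168 × 5 / 4.6 = 11.4, which gives power of about 0.81. N = 168 is the smallest multiple of 4 reaching 0.80 for ρ from 0.90 to 0.92. Other values of ρ give other sizes: 112 at 0.5, 140 at 0.7 and 152 at 0.8. The interaction formula, λ = f²·N·m / (1 − ρ) with 12 df, gives 32 at ρ = 0.5 and 12 at ρ = 0.9. So 168 is a between-group calculation, not an interaction one. Drop-out: 42/0.8 = 52.5, rounded up to 53, and 4 × 53 = 212. This agrees with the protocol.

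**2. Degrees of freedom.** Group: 4 − 1 = 3. Interaction: (4 − 1)(5 − 1) = 12.

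**3. Compare the two tests under one pattern of effect.** Let B, C and D be better than A by d SD at T2 to T5, with no difference at baseline.

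- Averaged over five visits the difference is 0.8d. The standard deviation of the four group means is 0.8d × √3/4 = 0.346d. So d = 0.5 is f = 0.173, and f = 0.25 needs d = 0.72.
- Group: λ = 42 × 5 × (0.64d² × 0.75) / (1 + 4ρ) = 100.8d² / (1 + 4ρ).
- Interaction: λ = 42 × (0.75d²) × 0.8 / (1 − ρ) = 25.2d² / (1 − ρ).

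A higher correlation weakens the group test and strengthens the interaction test. The table gives noncentralities from these formulas and rejection rates by noncentral F or simulation (3,000 to 6,000 runs per setting).

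| Effect | ρ | λ group | λ interaction | Group significant | Interaction significant | Group significant, gate shut |
|---|---|---|---|---|---|---|
| f = 0.25 (d = 0.72) | 0.3 | 23.9 | 18.8 | 99% | 83% | 17% |
| | 0.5 | 17.5 | 26.3 | 95% | 95% | 5% |
| | 0.7 | 13.8 | 43.8 | 88% | 100% | 0.2% |
| | 0.9 | 11.4 | 131 | 81% | 100% | 0% |
| f = 0.17 (d = 0.5) | 0.3 | 11.5 | 9.0 | 82% | 44% | 45% |
| | 0.5 | 8.4 | 12.6 | 67% | 61% | 26% |
| | 0.7 | 6.6 | 21.0 | 56% | 88% | 7% |
| | 0.9 | 5.5 | 63.0 | 47% | 100% | 0% |

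An additive pattern, with D equal to the sum of the B and C effects, gives nearly the same closed-gate rates: about 17%, 5%, 0% and 0% at f = 0.25.

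**4. Effect on a named contrast.** Take B vs A at T3 with d = 0.5 and Bonferroni over the four named contrasts (0.05/4 = 0.0125). Power is about 40% without the gate, and 19%, 27% and 36% with it at ρ = 0.3, 0.5 and 0.7. At f = 0.25, with Bonferroni over all six pairs, ungated and gated power were 71% and 61%, 75% and 71%, 73% and 73%, and 73% and 73% at ρ = 0.3, 0.5, 0.7 and 0.9. The gate therefore costs about 10, 4, 0 and 0 points. The spread in the ungated figures is simulation error.

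**The case against.** Four arguments stand against the point.

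- **The interaction is a sensible test here.** Baseline is one of the five measures and is randomised, so a differing change from baseline is what the interaction picks up, while the group main effect is diluted by the null baseline visit. This stands. At 0.5 SD and ρ = 0.7 the interaction alone is significant in about 39% of trials, against 7% for the group effect alone. A reader might infer that the interaction is irrelevant to the aims; it is not. What remains is that a 12-df test across all arms and visits is not any of the four named contrasts, and they need not wait for it.
- **The 45% and 26% figures do not describe the planned effect.** A reader might take them as the risk to the effect the trial was sized to detect. They belong to f = 0.17. At f = 0.25 the corresponding figures are 17% and 5%, and near ρ = 0.9, the only region that reproduces 168, they are nil. This stands. However, ρ is inferred from the sample size rather than stated, so lower values cannot be ruled out.
- **"Only" is a reading of the text.** Simple effects are the usual follow-up to an interaction, and the Bonferroni sentence could cover pairwise tests after a significant group effect, perhaps set out in an analysis plan not shown. This stands in part: such tests are not excluded, but none is specified, and the rule that is written makes the comparisons conditional.
- **Not every aim is wholly gated.** A reader might infer that all three aims can go entirely untested. Aim 1 also covers safety, and adverse events go to a chi-square or Fisher test without the gate, although that is a four-group test rather than D vs B or D vs C. The point is therefore limited to the efficacy contrasts on continuous outcomes.

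**Conclusion.** The point holds in a limited form. The text makes the pairwise efficacy contrasts of Aims 1 to 3 conditional on a 12-df interaction and sizes the trial on a 3-df group effect, so a significant group effect can be left without any reported efficacy contrast. How often depends on an unstated correlation and on the size of the effect. At the planned f = 0.25 it is 17% of trials at ρ = 0.3, 5% at 0.5 and practically none from 0.7 upward. For 0.5 SD it is 45%, 26%, 7% and none at ρ = 0.3, 0.5, 0.7 and 0.9. These figures assume 42 evaluable per arm, compound symmetry, equal baselines and a constant effect after baseline.

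The documents do not support the stronger claim that the plan is likely to miss the effect it was sized on. The reason to change the wording is that the gate is unnecessary alongside Bonferroni and can withhold estimates the aims call for.

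**What to change.** Two additions are needed, because the article names no primary visit.

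1. Name one of the scheduled post-baseline visits as primary for WOMAC.
2. Replace the conditional sentence with, for example: *The four contrasts of Aims 1 to 3 (D vs B, D vs C, B vs C, B vs A) are pre-specified. For WOMAC they will be estimated from the model at the primary visit, with confidence intervals and Bonferroni adjustment across the four, whatever the result of the group-by-time interaction or the group main effect. The interaction test describes the time course.*

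This needs no extra patients or assessments. The extra omnibus protection is lost, but testing each contrast at 0.05/4 = 0.0125 still holds the familywise error for these four at 0.05. The change does not make the contrasts well powered: with 42 per arm and 0.5 SD at one visit, ungated power is about 42% at 0.0125 by the standard two-mean formula.
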